## 2. Materials and Methods

### 2.1. Design

A randomized single-blind, parallel-group, controlled clinical trial performed on patients with coronary heart disease who underwent a percutaneous coronary intervention (PCI) with stent placement in the Cardiology Service of a public reference hospital complex providing specialist care in the province of Cadiz, Spain, in which 1500 coronary interventions procedures are performed per year (Figure 1).

### 2.2. Randomization and Blinding

The randomization and allocation to each group (1:1, intervention and usual care) are based on computer-generated random numbers. The researchers responsible for the study do not participate in the allocation of the participants. Due to the kind of intervention, blinding is not possible when the participants are allocated to groups. To minimize any bias, objective clinical variables are measured in the evaluation visit and the analyses are performed by blinded researchers.

### 2.3. Study Sample

The participants are eligible to participate if they have a confirmed diagnosis of coronary heart disease and undergo stenting with PCI. Furthermore, the participants must comply with the following criteria.

#### 2.3.1. Inclusion Criteria

Adults over 18 and below 75 years of age who have a smartphone that can receive messages and connect to the internet throughout the study period.

#### 2.3.2. Exclusion Criteria

Severe heart failure, physical disability or dementia and severe congenital, structural or rheumatic heart disease, chronic kidney or liver disease, if they are already using a health-monitoring application, or the application is not compatible with their telephone.

### 2.4. Sample Size

To detect a medium effect size of Cohen’s d of 0.5 [32] regarding adherence to the Mediterranean diet (8.6 ± 2.0 puntos) [33], food consumption, vegetables (471.4 g/day ± 230.0 g/day), fruit (308.4 g/day ± 188.6 g/day), meat and derived products (149.7 g/day ± 63.7 g/day), fish (122.3 g/day ± 73.5 g/day) [34], physical activity (210.2 METs-min/day ± 221.8 METs-min/day) [35,36] and a 12% decrease in smoking habits (prevalence of 21% in pilot study), a 95% confidence interval and a power of 90%, the sample size is estimated at 100 patients in each group. Assuming a 20% loss to follow-up with 240 participants, 120 in each arm: intervention and usual care.

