#### 3.2.1. Primary Outcome Variables

The primary outcome measures after nine months in both groups will be changes in behavior relating to 1. Healthy diet: Adherence to the Mediterranean diet and average intake of each food group. 2. Level of physical activity (MET) and the number of steps per day, and a less sedentary lifestyle. 3. Smokers stop smoking. 4. Treatment Adherence. 5. Knowledge acquired. 6. Usability and satisfaction with the application.

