### 3.3. Statistical Analysis

The principles of intention-to-treat analysis will be followed. The differences between patients who gave up the app and those who were able to utilize it will also be examined by analyzing the outcome variables from the electronic medical record. A descriptive statistical analysis will be performed (mean, standard deviation, 95% confidence interval, frequencies, and percentages). For the comparison of means, the Student’s t-test will be used (normal distribution variables) and the Mann–Whitney U test (if the variables are non-normally distributed). The Chi-squared/Fisher test will be used for the comparison of proportions. The relative risks and 95% confidence intervals will be computed. The quantitative primary outcomes from the two groups will be compared using an analysis of covariance adjusted for age and gender. A sensitivity analysis will also be performed regarding the baseline characteristics of the participants in both groups and missing data. A multivariate analysis will be performed to examine the association of the intervention with lifestyle habits, control of the CVRFs and evolution after discharge regarding cardiovascular events, the use of health services, emergency visits, and readmissions using Kaplan–Meier survival analysis. A two-tailed *p*-value < 0.05 will be considered statistically significant. The SPSS v.24.0 software will be used. 24.0. The researchers analyzing the results will be blinded to the allocation of the participants.

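### Section 2.4 states 90% power for the smoking target, but its printed inputs, read plainly as 21% against 9%, give about 66% with 100 per arm (61% by Fisher's test)

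*Protocol article*

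**What the plan says.** Section 2.4 (Sample Size) opens with "To detect a medium effect size of Cohen’s d of 0.5" for Mediterranean-diet adherence, the food groups and physical activity. The same sentence then adds "a 12% decrease in smoking habits (prevalence of 21% in pilot study), a 95% confidence interval and a power of 90" per cent, and concludes that "the sample size is estimated at 100 patients in each group". It allows for 20% loss by enrolling 120 per arm. One number of patients and one power therefore apply to both kinds of target.

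Section 3.2.1 lists "Smokers stop smoking" among the primary outcomes at nine months. Section 2.2 sets 1:1 allocation. Section 3.3 plans a chi-squared or Fisher test for proportions and says that a two-tailed p-value below 0.05 "will be considered statistically significant".

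Section 2.4 does not say whether the 12% is absolute or relative, whether the denominator is all participants or baseline smokers, or what smoking rate is expected under usual care at nine months. The 21% is described only as the prevalence in the pilot study.

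**The concern.** A proportion falling from 21% to 9% is a smaller standardised effect than d = 0.5 (about 0.34 on the arcsine scale), so one sample size is unlikely to give both targets the same power. The power sentence prints every number needed for a first check, and that check does not return 90%.

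Smoking is a declared primary outcome and is named in the sample-size justification. If the plain reading is the intended one, a true 12-point reduction would be missed about one time in three (about four in ten by Fisher's test), not one time in ten. A reader relying on the printed 90% could then give a non-significant smoking result more weight than the design supports.

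**Working it through.** **Inputs.** p1 = 0.21, a decrease of 12%, 90% power, 95% confidence and 100 per arm, all from section 2.4. 1:1 allocation from section 2.2. Two-sided 0.05 and chi-squared or Fisher from section 3.3. Assumption: the decrease is absolute and in all participants, so p2 = 0.09. The document does not say so.

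**The continuous target, where the plan's figure holds.** n per arm = 2 × [(1.960 + 1.2816)/0.5]² = 84.1, so 85 (85.03 by the t-test). Power at 100 per arm is 94%, and at 96 per arm 93%. The 100 per group is adequate for d = 0.5.

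**The smoking target, plain reading.** With p̄ = (0.21 + 0.09)/2 = 0.15,

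n = [1.960·√(2·0.15·0.85) + 1.2816·√(0.21·0.79 + 0.09·0.91)]² / 0.12²
= (0.9897 + 0.6380)² / 0.0144 = 183.98, so 184 per arm.

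The same formula gives 138 per arm for 80% power. Solving it for power at n = 100:

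z = [0.12·√100 − 0.9897] / √(0.1659 + 0.0819) = 0.2103/0.4978 = 0.422, power 66.4%.

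The 20% loss from 120 leaves 120 × 0.8 = 96 per arm, so that case is shown too:

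| Evaluable per arm | Chi-squared formula | Exact chi-squared | Fisher |
|---|---|---|---|
| 100 | 66.4% | 67.8% | 60.8% |
| 96 | 64.6% | 65.7% | 58.6% |
| 120 (no losses) | 74.3% | 75.5% | 69.0% |

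**Other readings of the same words, 100 per arm.**
- Relative decrease, 21% to 0.21 × 0.88 = 18.5%: power 6.5%, and 5,241 per arm for 90%.
- Fall *to* 12%: power 40%, and 356 per arm for 90%.
- One-sided 5% for 21% against 9%, contrary to section 3.3: power 77%.

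**Readings that do reach 90%.**
- *Cessation among baseline smokers, keeping a 12-point gap in overall prevalence.* About 21 smokers per arm (21% of 100), and 12/21 = 57 points difference in quit rates. Fisher power is above 99.9% if no usual-care smoker quits, and 97%, 95%, 96% and 99% for usual-care quit rates of 10%, 20%, 30% and 40%.
- *All participants, with quitting in usual care too and the 12-point gap kept.* By the formula: 18.9% against 6.9% gives 72%, 15.75% against 3.75% gives 82%, and 13.6% against 1.6% gives 90%. The last pair means that (21 − 13.6)/21 = 35% of usual-care smokers and (21 − 1.6)/21 = 92% of intervention smokers stop.
- *Tests other than the planned one.* A within-group McNemar test with 13% stopping and 1% starting needs 98 per group, and a one-sample test of 9% against 21% needs 95. Neither compares the randomised groups.

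**Smokers only, with 12 points taken as the difference in quit rates.** With 21 smokers per arm and usual-care quit rates of 0% to 40%, Fisher power is about 6% to 11%.

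**The case against.** The strongest reply is that 21% against 9% in all participants may not be the comparison the trial intends. The primary outcome is smokers stopping, baseline smoking is recorded, and section 3.1 has cessation confirmed by exhaled carbon monoxide, so baseline smokers are a natural denominator. In that group a 12-point fall in overall prevalence is a 57-point difference in quit rates, and about 21 smokers per arm give more than 90% power. Section 2.5 also gives both arms written advice to stop smoking, so a usual-care rate still at 21% is itself an assumption. A lower one raises the power of a 12-point gap.

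These calculations are correct, and they limit the point. A reader might infer that 21% against 9% is the most favourable reading, or that 100 per arm cannot give 90% power for smoking under any reading. The documents support neither, because they leave the denominator and the usual-care rate open.

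The reply does not rescue the sentence as printed. Section 2.4 states no 57-point quit-rate difference, no smokers-only denominator and no usual-care quit rate. If the smokers-only denominator is right but the 12% is the difference in quit rates, power is about 6% to 11%.

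It is also fair to say that an article condenses a longer protocol, which may hold the missing assumptions. That would excuse an omission. Here a power is printed beside inputs that, taken at face value with the stated test, do not produce it.

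**Conclusion.** The 90% power in section 2.4 is supported for the continuous outcomes at d = 0.5 and not, from what is printed, for smoking. On the plain reading, power is about 66% with 100 per arm (61% by Fisher) and about 65% with 96 (59% by Fisher), and 184 per arm would be needed for 90%. On a relative reading it is about 6.5%.

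These figures rest on taking the 12% as absolute, all participants as the denominator and 21% as the usual-care rate at nine months. That is an interpretation. Power of 90% or more is possible under other assumptions, but they have to be supplied from outside the text and are demanding: a quit-rate difference of roughly 57 points among smokers, or substantial quitting in usual care with the full 12-point gap kept. The power for diet and activity at d = 0.5 is unaffected.

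**What to change.** In section 2.4:

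1. Limit the 90% power statement to the continuous outcomes at d = 0.5 (85 per arm needed, 94% power at 100).
2. For smoking, state whether the 12% is absolute or relative, whether the denominator is all participants or baseline smokers, and the smoking or quit rate assumed under usual care at nine months.
3. Report the power that follows and name the test. If 21% against 9% of all participants is what was meant, that is about 65% to 66% by the chi-squared formula and 59% to 61% by Fisher's test, with 96 to 100 per arm. If a smokers-only comparison was meant, give the number of smokers expected per arm and the quit rates assumed in both arms.

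The cost is a few sentences, and probably a less favourable power figure for one primary outcome. No extra patients are needed, and the planned 240 stands.

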### 2.5. Recruitment

After the PCI and during admission, the nurse will recruit eligible patients and their care partners, will ask them to sign the informed consent, perform the initial assessment and organize a programmed visit after 36 weeks. A card will be provided with the date of the appointment and a telephone number for any changes.

The participants allocated to the usual care group receive the standard prescribed care and advice about medication, and lifestyle.

Both groups will be provided with written recommendations and an explanation about the standard Mediterranean diet, physical activity, stopping smoking and treatment adherence.

Before hospital discharge, all the patients will be encouraged to follow a healthy lifestyle. Stages of change strategies will be used in addition to a motivational and behavior changing interview [37,38]. Written information will be provided about risk factors, lifestyle goals, a suggested healthy menu, recommendations about the daily intake of food groups [39], and the other behavior that the intervention is targeting.

Currently, this study has recruited 95 patients.

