### 2.6. Intervention

The intervention begins during the patient’s stay in hospital immediately after a coronary event. The participants from the intervention group and their partner/carer will complete a short online tutorial describing the mobile application accessed using a mobile telephone or tablet (Figure 2). They will be advised to use the application for at least 15 min per day. This time has been considered sufficient for the daily recording of data in the pilot study. The intervention will last 36 weeks. If the patient does not record data for a week, he/she receives a message through the app encouraging him to use it. The patients may resolve any queries using the application’s built-in messaging function, to which the nurse will reply through this messaging service or with a telephone call. This avoids many patient visits to the doctor for consultations and reduces human resource needs.

Before the trial, a pilot study was performed with 20 participants to test the application and make any necessary adjustments.

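### The smoking target in section 2.4 rests on one undated pilot rate, allows for no quitting in usual care, and has about 66% power at 100 per group rather than the stated 90%

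*Protocol article*

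**What the plan says.** Section 2.4 (Sample Size) covers several outcomes in one sentence. The continuous ones are planned on a standardised difference: "To detect a medium effect size of Cohen’s d of 0.5". Smoking is planned on "a 12% decrease in smoking habits (prevalence of 21% in pilot study"). One conclusion is drawn for all of them: "a 95% confidence interval and a power of 90%, the sample size is estimated at 100 patients in each group". Enrolment is then set at 120 per arm for a 20% loss. Section 3.3 sets the test level: "A two-tailed *p*-value < 0.05 will be considered statistically significant".

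The only pilot described is in section 2.6: "Before the trial, a pilot study was performed with 20 participants to test the application". No control arm is mentioned for it.

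Section 2.5 (Recruitment) describes what usual care receives: "Both groups will be provided with written recommendations and an explanation about the standard Mediterranean diet, physical activity, stopping smoking and treatment adherence". It adds that, before discharge, all patients get encouragement, stages-of-change strategies and a motivational interview. Section 3.2.1 lists stopping smoking, among smokers, as a primary outcome at nine months in both groups.

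**The concern.** A two-group calculation for smoking needs two nine-month rates, one per arm. Section 2.4 gives one rate and one decrease. The natural reading is 21% in usual care and 9% on the app. That makes usual care a group in which smoking does not fall, yet section 2.5 shows it receives cessation advice and a behaviour-change interview straight after a coronary procedure. If some usual-care smokers stop, the usual-care rate at nine months lies below the starting prevalence and there is less room for a difference.

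The 90% power is stated for a primary outcome. If the real power is much lower, a null smoking result could be read as failure of an adequately planned test when the trial had little chance of showing a worthwhile effect.

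**Working it through.** **Inputs.** Prevalence 21%, decrease 12%, 90% power and 100 per group come from section 2.4; two-sided 5% comes from section 3.3; 1:1 allocation from section 2.2. Usual-care quit rates are assumptions, because the document gives none.

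**1. The stated figure for the continuous outcomes.** n = 2 × ((1.960 + 1.282)/0.5)² = 84.1, so 85 per group. With 100 per group the power is 94%. The stated 100 therefore covers d = 0.5.

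**2. The stated figure for smoking, absolute reading (21% vs 9%).** Mean rate 0.15; pooled term √(2 × 0.15 × 0.85) = 0.505; unpooled term √(0.21 × 0.79 + 0.09 × 0.91) = 0.498.

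- n = (1.960 × 0.505 + 1.282 × 0.498)² / 0.12² = 184 per group (201 with a continuity correction, 179 by the arcsine method).
- Power at 100 per group: z = (0.12 − 1.960 × 0.0505)/0.0498 = 0.42, so 66%.
- Power at 96 per group (120 × 0.8, after the stated loss): 65%.

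Changing to 80% power (138) or to a one-sided test (150 at 90% power, 109 at 80%) does not give 100 either.

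**3. The relative reading (21% vs 0.88 × 21% = 18.5%).** This needs about 5,241 per group at 90% power. At 100 per group the power is about 7%.

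**4. What the absolute target asks of smokers.** With 21% smoking at baseline in each arm, a 12-point gap means 12/21 = 57 percentage points more of the smokers quitting on the app than in usual care. If a share q of usual-care smokers quit, the app arm must reach q + 57%: 67% at q = 10%, 77% at q = 20%, 87% at q = 30%. The gap becomes impossible only when q exceeds 1 − 12/21 = 43%.

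**5. Power when usual care also quits.** Keep the planned ratio of the two rates, 9/21, with usual-care prevalence 21% × (1 − q) and 100 per group:

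| Assumed usual-care quit rate | Usual care vs app | Power |
|---|---|---|
| 0% | 21.0% vs 9.0% | 66% |
| 10% | 18.9% vs 8.1% | 61% |
| 20% | 16.8% vs 7.2% | 55% |
| 30% | 14.7% vs 6.3% | 49% |

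If a full 12-point gap persisted instead, power would rise as the rates fall (72%, 79% and 86% at 10%, 20% and 30%), but only with the app quit rates in step 4. The cost of usual-care quitting thus falls on feasibility if the gap is fixed, and on power if the ratio is fixed.

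**6. What 100 per group can detect with 90% power, from a 21% baseline.** With no usual-care quitting, about 21% vs 5.6%, which means 1 − 5.6/21 = 73% of app-arm smokers quitting. With 20% usual-care quitting, about 16.8% vs 3.2%, or 1 − 3.2/21 = 85%.

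**7. Source of the 21%.** 0.21 × 20 = 4.2, so 21% is not a whole count out of 20; 4/20 is 20% and 4/19 is 21.1%. Section 2.4 gives no denominator. The exact 95% interval for 4/20 is 6% to 44%.

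**The case against.** The strongest reply is that the document says less than a critic may read into it. A reader might infer that the 21% is a pre-treatment prevalence knowingly used as the nine-month usual-care rate. The text gives neither time point nor arm, so that is only an inference. A reader might also infer that the target is unattainable. The documents do not support that: the 43% is a break-even point, no usual-care quit rate is given, and at 10% or 20% usual-care quitting the target is demanding but possible. On a relative 12% the impossibility does not arise at all. These replies stand. None of them restores the 90% power, which fails on both readings before any usual-care quitting is assumed.

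The odd pilot figure is weak evidence of error, since one missing value among 20 would explain it. What remains is that a rate from about 20 people is imprecise.

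It can also be said that a condensed article may leave the rationale for a planning rate to the full protocol. That would excuse a missing rationale. It does not excuse a stated power that the stated figures do not give.

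Finally, 100 per group is enough for the d = 0.5 outcomes, so the sample size does not depend on smoking. This is correct and limits the consequence to what the trial may claim about smoking.

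**Conclusion.** The point holds in a limited form. The smoking target is under-specified and makes no allowance for cessation in usual care, and its stated 90% power is not delivered. On the absolute reading, power is about 66% at 100 per group and 65% at 96. With the relative effect held at 9/21, it falls to between 61% and 49% for usual-care quit rates of 10% to 30%. On the relative reading, the sample is far too small.

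The 66% rests on the plan's own figures, an absolute 12 points, and a two-sided test of two proportions. The lower figures also rest on the assumed quit rates and on 21% being the baseline prevalence in both arms. The working does not show that the target will fail, only that it is demanding and that the power claimed for it is wrong.

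**What to change.** In section 2.4:

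- Withdraw the 90% power claim for smoking and keep it for the d = 0.5 outcomes.
- State that the smoking difference is between arms at nine months, whether it is absolute or relative, and what the 21% refers to.
- Take baseline smoking prevalence, tabulated without regard to arm, from the patients already enrolled (section 2.5: "Currently, this study has recruited 95 patients") in place of the pilot figure.
- Report the difference detectable at the existing sample size over a stated range of usual-care quit rates, with the usual-care rate set at baseline prevalence × (1 − quit rate). Give the corresponding quit rates among smokers, since section 3.2.1 defines the outcome as smokers stopping. The two cases in step 6 of the working show the form. The range is an assumption and should be labelled as one.

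The cost is wording, one blinded tabulation of baseline data, and a less favourable stated sensitivity for smoking. No extra patients and no unblinding are needed.

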## Abstract

Coronary heart disease is one of the main causes of morbimortality around the world. Patients that survive a coronary event suffer a high risk of readmission, relapse and mortality, attributed to the sub-optimal control of cardiovascular risk factors (CVRF), which highlights the need to improve secondary prevention strategies aimed at improving their lifestyle and adherence to treatment. Through a randomized controlled clinical trial, this study aims to evaluate the effect of an intervention involving an online health application supported by a mobile telephone or tablet (mHealth) on lifestyle (diet, physical activity, and tobacco consumption) and treatment adherence among people with coronary heart disease after percutaneous coronary intervention. The sample will comprise 240 subjects (120 in each arm: intervention and usual care). They are assessed immediately and nine months after their hospital discharge about sociodemographic, clinical, CVRF, lifestyle, and treatment adherence characteristics. The educative intervention, involving a follow-up and self-monitoring, will be performed using an online mHealth tool consisting of an application for mobile phones and tablets. The quantitative primary outcomes from the two groups will be compared using an analysis of covariance (ANCOVA) adjusted for age and gender. A multivariate analysis will be performed to examine the association of the intervention with lifestyle habits, the control of CVRFs, and outcomes after discharge in terms of the use of health services, emergency visits, cardiovascular events and readmissions.

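### With the stated 20% loss, 120 per arm leaves 96 patients rather than the stated 100; the d = 0.5 outcomes keep 90% power, but the figures need restating and smoking must be handled separately

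*Protocol article*

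**What the plan says.** Section 2.4 of the protocol article gives the sample size in two sentences. The first lists the targets: for the diet, food-consumption and physical-activity measures, "To detect a medium effect size of Cohen’s d of 0.5"; for smoking, "a 12% decrease in smoking habits (prevalence of 21% in pilot study"). All are placed under "a 95% confidence interval and a power of 90" per cent, and the result is that "the sample size is estimated at 100 patients in each group". The second sentence moves from requirement to enrolment: "Assuming a 20% loss to follow-up with 240 participants, 120 in each arm: intervention and usual care".

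The Abstract repeats the enrolment figure ("The sample will comprise 240 subjects (120 in each arm: intervention and usual care"), and section 2.2 gives the allocation ratio as 1:1. Section 3.3 sets a two-tailed 5% significance level. The article shows no inflation formula, no other loss rate and no other reason for 120 per arm.

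**The concern.** Requirement, loss rate and enrolment stand in adjacent sentences, so each can be checked against the other two. An allowance for loss to follow-up exists so that the required number remains after the assumed loss. Here it does not: if the trial loses exactly the fifth it planned for, it ends below its own stated need. A report giving 96 per arm against a stated 100 would look underpowered, although for most of the listed outcomes it would not be.

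This is not detail left to a fuller document. All three figures are printed, and they are inconsistent. What has to be settled is the size of the mismatch, and whether it costs any listed outcome its 90% power.

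**Working it through.** **Inputs.** Required per group: 100. Loss: 20%. Enrolment: 120 per arm, 240 in total. Effect sizes: d = 0.5 for the continuous outcomes; a 12% decrease from 21% for smoking. Power: 90% (all section 2.4). Two-sided 5% (section 3.3). Allocation 1:1 (section 2.2).

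**1. Reproducing the stated enrolment.**
- n × (1 + loss) = 100 × 1.20 = 120. This matches the article.
- n / (1 − loss) = 100 / 0.80 = 125 per arm, 250 in total. This does not match.

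**2. What 120 per arm delivers.**
- Remaining after 20% loss: 120 × 0.80 = 96 per arm, 192 in total.
- Gap in evaluable patients: 100 − 96 = 4 per arm, 8 in total.
- Gap in randomised patients: 250 − 240 = 10 in total.
- Largest loss that still leaves 100: 1 − 100/120 = 16.7%.

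**3. Continuous outcomes at d = 0.5.**
- Normal approximation: n = 2(1.960 + 1.282)² / 0.5² = 84.1, so 85 per arm.
- t-test: 85.03, so 86 per arm.
- Randomised per arm needed to keep 86 after 20% loss: 86 / 0.80 = 107.5, so 108. The planned 120 covers this.
- Power by the t-test: 93.1% at 96 per arm, 94.0% at 100.

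**4. Smoking.** The text does not say whether the 12% decrease is absolute or relative, so both readings are shown. The formula is the usual comparison of two proportions without continuity correction, with all patients in each arm as denominator:

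power = Φ{ [Δ√n − 1.960√(2p̄(1 − p̄))] / √(p₁(1 − p₁) + p₂(1 − p₂)) }

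- Absolute, 21% vs 9% (Δ = 0.12, p̄ = 0.15), n = 96: (1.176 − 0.990) / 0.498 = 0.374, power 64.6%. At n = 100: (1.200 − 0.990) / 0.498 = 0.422, power 66.4%. For 90% power, 184 evaluable per arm are needed.
- Relative, 21% vs 18.5% (0.21 × 0.88 = 0.1848, Δ = 0.0252), n = 96: (0.247 − 1.103) / 0.563 = −1.52, power 6.4%. At n = 100, 6.5%. For 90% power, about 5,241 per arm are needed.

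On either reading, moving from 96 to 100 evaluable patients changes smoking power by less than two percentage points. Enrolling 125 per arm would not repair that outcome.

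**The case against.** The strongest objection is that almost nothing follows from the mismatch. For the d = 0.5 outcomes, power falls by under one percentage point and stays above 90%. The figure that is missed, 100, is itself more than those outcomes need. This stands, and it limits the point to a minor one for those outcomes. It does not remove the point, because the stated figures still contradict each other.

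A second defence is that the 20% was meant as a share of the 100 retained, that is, 20 lost out of 120. Loss to follow-up is ordinarily a share of those enrolled, and the article does not say otherwise. If that was the intention, the loss allowance is 20/120 = 16.7% and should be stated so.

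Third, it is tempting to say that the plan multiplied by 1.20 where it should have divided by 0.80. That is the likely explanation, since it reproduces 120 exactly, but no formula is shown, so it remains an inference.

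Fourth, a remedy that speaks only of d = 0.5 could make the whole section look sound. This also stands. The 90% claim covers smoking as well, and reassurance about enrolment cannot be extended to it.

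**Conclusion.** The inconsistency is real. At the stated 20% loss, 120 per arm leaves 96 evaluable patients, 4 fewer than the stated 100, and 125 per arm would be needed to keep 100. This rests only on the article's own figures and on reading the loss as a share of those randomised.

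For the continuous outcomes at d = 0.5 it is minor: 96 exceeds the 86 needed, and power is 93%.

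A reader might infer two stronger things that the documents do not support.
- That the trial must enrol 250, or is underpowered because of this slip. The shortfall is against the stated 100, not against 90% power at d = 0.5.
- The opposite, that 240 is therefore adequate for everything listed. It is not shown to be adequate for smoking, where power at 96 per arm is about 65% on the absolute reading and about 6% on the relative one. Both readings are assumptions. Section 3.2.1 also words the outcome in terms of smokers quitting, which may restrict the denominator to smokers; the figures here use all patients. The loss allowance did not cause the smoking gap, and correcting it would not close it.

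**What to change.** Leave enrolment as it is for the d = 0.5 outcomes and replace the second sentence of section 2.4 with wording such as:

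*240 patients will be randomised; with 20% loss to follow-up, 96 per arm will be evaluable. For the continuous outcomes at d = 0.5 (two-sided 5%), 86 per arm are needed for 90% power, and 96 give 93%.*

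Alternatively, keep 100 evaluable per arm and give the loss allowance as 16.7%.

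In either case, take smoking out of the shared 90% claim and deal with it in its own sentence: say whether the 12% decrease is absolute or relative, name the denominator, and report the power that follows.

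The cost is one corrected sentence and one separate statement on smoking. The Abstract's 240 can stand. Section 2.5 reports 95 patients recruited so far, so the text can be corrected well before follow-up is complete.
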